At present, despite the fact that the Chinese Glaucoma Guideline (2020) has recommended slit lamp microscopy, IOP measurement, and fundus examination as routine glaucoma screening methods (5), the cost-effectiveness of these approaches in screening remains uncertain. Consequently, there is also an urgent need to develop a glaucoma screening model that is cost-effective, scalable, and suited to the national context. Furthermore, rapid economic and technological advances have facilitated the widespread adoption of telemedicine and artificial intelligence (AI), offering innovative approaches to glaucoma screening (13). Specifically, AI-assisted diagnosis and follow-up can markedly improve screening efficiency and quality, reduce dependence on specialists, and save considerable time and financial resources, potentially leading to a more effective, convenient, and cost-effective screening model (14–17).

Therefore, this study intends to conduct a cluster randomized controlled trial with a 6-year follow-up to establish and validate an AI-assisted three-tiered glaucoma screening model based on the community population, assess its cost-effectiveness, and evaluate the performance of AI-assisted diagnostic tools, thereby generating evidence to inform future optimization.

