### Grouping schemes

2.4

According to the cluster randomized study design, each community serves as a cluster. The statistician uses a computer-generated random sequence to independently and with equal probability assign each cluster to one of the three groups (simple cluster randomization): (1) blank control group (no screening group), (2) routine screening group, and (3) tiered screening group. To set up blank controls can analyze the clinical significance and health economic value of routine screening mode for the early diagnosis and treatment of glaucoma. On this basis, it is sufficient to compare the difference in efficiency and cost-effectiveness between the routine screening mode and the tiered screening mode. Baseline data and follow-up outcomes are collected uniformly for all participants.

The control group (no screening group) does not undergo any glaucoma screening, and the study subjects can detect and confirm glaucoma through active medical visit or opportunistic screening. The routine screening group is screened with IOP measurement combined with fundus photography to detect glaucoma. The three-tiered screening model designed in this study is adopted in the tiered screening group. It is expected that high-risk populations of glaucoma are identified in the tier 1 screening, who will enter the tier 2 and/or 3 screenings to diagnose or exclude glaucoma (Figure 1).

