Secondary outcome measures include comparative analyses of the cost-effectiveness of different screening strategies and the diagnostic accuracy of physician-based versus AI-assisted image interpretation in fundus photography for screening glaucoma. The comparison of diagnostic accuracy will be evaluated at the per-participant level and will include sensitivity and specificity, as well as AUC for each interpretation method.

The cost-effectiveness analysis will be conducted from a societal perspective to comprehensively evaluate the resources consumed and health outcomes generated by different screening strategies. The primary economic outcome is the incremental cost-effectiveness ratio (ICER), expressed as the incremental cost per additional glaucoma case detected (based on observed data within the study period), and the incremental cost per quality-adjusted life year (QALY) gained (based on long-term model extrapolation). Cost components will encompass screening-related expenses, including personnel, equipment, consumables, site costs, and AI-assisted interpretation fees; diagnostic confirmation costs following referral, such as OCT and automated perimetry; subsequent treatment and follow-up costs; and direct non-medical and indirect costs, including transportation expenses and productivity losses incurred by patients and their families. Health utility values will be measured prospectively among diagnosed patients during follow-up using the EQ-5D-5L instrument and converted to utility weights using the Chinese value set. Costs and effects within the study period will be obtained through actual data collection, whereas long-term outcomes will be evaluated using a Markov state-transition model simulating the natural history of glaucoma and the long-term trajectory following screening intervention. The model will employ a cycle length of 1 year and a lifetime horizon, and future costs and health outcomes will be discounted to present value at an annual rate of 3%. Uncertainty in the incremental analysis will be assessed through one-way sensitivity analyses and probabilistic sensitivity analysis, and cost-effectiveness acceptability curves will be generated to illustrate the probability that the tiered screening strategy is cost-effective across a range of willingness-to-pay thresholds.

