## Discussion

4

This study aims to conduct a community-based cluster randomized controlled trial to evaluate the feasibility, effectiveness, and cost-effectiveness of a systematic three-tiered screening strategy for glaucoma. Irreversible visual impairment is the hallmark of glaucoma as the leading cause of irreversible blindness worldwide, a tragic outcome largely attributable to delayed diagnosis. Although the necessity of glaucoma screening is widely acknowledged within the academic community, key questions regarding “how to screen,” “where to screen,” and “which populations to target” remain unresolved without a unified optimal pathway. Current hospital-based opportunistic screening models have limited coverage, while some previous population-based studies, despite providing valuable epidemiological data, have encountered major challenges in the feasibility and sustainability of their complex examination protocols (such as requiring all participants to undergo visual field testing) in real-world community settings (27, 28).

The superiority of the three-tiered screening protocol designed in this study lies in its establishment of a more cost-effective and scalable tiered screening model. Previous research tended to employ relatively homogeneous examinations for broad populations (29), which entailed substantial resource consumption and demonstrated insufficient targeting of asymptomatic high-risk individuals. In contrast, this study proposes the use of a structured questionnaire in the tier 1 screening to identify high-risk individuals (e.g., aged > 40 years, with a family history, or with high myopia), thereby significantly narrowing the population base requiring secondary screening, and avoiding the inefficient pattern of conducting expensive examinations on all community residents. This approach aligns with the concept of exploring risk factors in the Singapore Epidemiology of Eye Diseases (SEED) study (30), while our protocol aims to further develop this concept into an operational screening tool, substantially enhancing the positive detection rate of subsequent examinations.

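### Section 2.4 calls tiered versus routine a sufficient economic comparison, while the Discussion expects a conclusion against both routine and no screening; no joint three-strategy analysis is stated

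*Protocol article*

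**What the plan says.** Section 2.4 (Grouping schemes) defines three arms and gives the no-screening arm a specific economic task, with glaucoma as the disease in question: "To set up blank controls can analyze the clinical significance and health economic value of routine screening mode for the early diagnosis and treatment of". Building on that first comparison, the section then adds: "it is sufficient to compare the difference in efficiency and cost-effectiveness between the routine screening mode and the tiered screening mode".

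Section 2.6 (Follow-ups and outcome variables) lists as a secondary outcome "comparative analyses of the cost-effectiveness of different screening strategies". It then states: "The primary economic outcome is the incremental cost-effectiveness ratio (ICER), expressed as the incremental cost per additional glaucoma case detected". A second ratio, per QALY gained, follows. No reference strategy is named for either ratio. The uncertainty analysis ends with: "cost-effectiveness acceptability curves will be generated to illustrate the probability that the tiered screening strategy is cost-effective across a range of willingness-to-pay thresholds". Again no comparator is named, and no curve is described for routine or for no screening.

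The last paragraph of the Discussion expects tiered screening to be more cost-effective than routine screening or no screening. Section 2.1 places cost-effectiveness among the main objectives, as a preliminary evaluation. Of the guideline-recommended routine methods, the Introduction says that "the cost-effectiveness of these approaches in screening remains uncertain".

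**The concern.** With three alternatives, showing that one beats a second does not show that it is worth doing. Routine screening is a safe stepping stone to tiered only if routine is itself good value against no screening. The protocol calls that an open question and still describes the next comparison as sufficient. It gives no further step for the case where routine fails.

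A decision-maker reading a high probability that tiered is cost-effective will take it as support for introducing tiered screening. If that probability was computed against routine alone, it answers a narrower question. The results are meant to inform guidelines, and the Discussion already anticipates the wider claim.

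**Working it through.** **What can be reproduced.** The protocol states no ICER, cost, QALY or threshold, so there is no economic figure to reproduce. The check has three parts: the logic of the chain, the cost order implied by Table 1, and an illustration on assumed inputs.

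**1. Logic.** Let net benefit be NB = threshold × QALY − cost. Then

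NB(tiered) − NB(none) = [NB(tiered) − NB(routine)] + [NB(routine) − NB(none)].

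If both brackets are positive, tiered beats no screening and the chain is right. Tiered can beat routine and still lose to no screening only when the second bracket is negative and larger in size than the first. So routine being poor value against no screening is a necessary condition for the error.

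**2. Cost order.** Table 1 schedules IOP and fundus photography at 3 visits (baseline, years 3 and 6) for everyone in the routine arm. In the tiered arm it schedules them at 7 visits (baseline and years 1 to 6) for high-risk participants and at none for the rest. With a high-risk share h, tiered uses fewer of these examinations per person if 7h < 3, that is h < 3/7 = 43%. This ignores questionnaires, biometry, referrals and removal after diagnosis. The protocol gives no value for h, so neither order of cost can be assumed.

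**3. Illustration (all inputs assumed; costs in CNY).** Values are per person, relative to no screening.

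In (a) and (b), cost has a CV of 15% and QALY a CV of 25%. The correlation between routine and tiered is 0.9 for cost and 0.9 for QALY, and cost and QALY are independent. In (c), each of the three strategies has an independent SD of 40 for cost and 0.0005 for QALY.

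- (a) Routine 300 and 0.0030; tiered 210 and 0.0030. Routine v none: 300/0.0030 = 100,000. Tiered v none: 210/0.0030 = 70,000. Tiered saves 90 against routine at equal QALY.
- (b) Routine 300 and 0.0020; tiered 360 and 0.0030. Routine v none: 300/0.0020 = 150,000. Tiered v routine: 60/0.0010 = 60,000. Tiered v none: 360/0.0030 = 120,000. Routine is extendedly dominated.
- (c) Routine 100 and 0.0020; tiered 150 and 0.0030. All three ratios are 50,000.

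| Case | Threshold per QALY | P(tiered beats routine) | P(tiered best of three) |
|---|---|---|---|
| (a) | 60,000 | 1.00 | 0.29 |
| (a) | 100,000 | 0.99 | 0.86 |
| (a) | 150,000 | 0.95 | 0.93 |
| (b) | 100,000 | 0.82 | 0.26 |
| (c) | 80,000 | 0.64 | 0.60 |

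Hand check of two entries, using P(tiered beats none), which nearly equals P(best of three) where routine is almost never best:

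- (a) at 60,000: mean net benefit is 180 − 210 = −30. The SD is √(45² + 31.5²) = 54.9, so z = −0.55 and P = 0.29.
- (b) at 100,000: mean net benefit is 300 − 360 = −60. The SD is √(75² + 54²) = 92.4, so z = −0.65 and P = 0.26.

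**What the two planned comparisons leave open.** In (a), at thresholds of 60,000 and 80,000 alike, routine fails against none (100,000) and tiered beats routine. Yet tiered v none (70,000) fails at the first threshold and passes at the second. The two pairwise verdicts are the same while the right choice differs.

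**The case against.** A reader might infer that the plan compares tiered with routine only and will draw a single curve. The text does not support that. Section 2.6 speaks of different strategies, leaves the ICER's reference open and refers to curves in the plural. Its wording is compatible with the probability that tiered is best of all three. The Discussion foresees a contrast with no screening. The sentence in section 2.4 can also be read as a rationale for having three arms rather than as an economic decision rule.

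A reader might also infer that tiered must be cheaper than routine, because the Discussion speaks of "avoiding the inefficient pattern of conducting expensive examinations on all community residents". That remark contrasts tiering with previous research, not with this trial's routine arm, and the 3/7 calculation shows that the order could go either way.

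Nor is the no-screening arm ignored. Routine versus none is planned, and the two steps add up to tiered versus none: in (a), 300 − 90 = 210. A careful reader of both results would see that routine was a poor comparator. The article describes the economic work as preliminary, and a fuller economic plan may exist.

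All of this limits the point without removing it. Point estimates can be added up, but the probability for tiered against none needs the joint draws. Calling one pairwise comparison sufficient is a positive statement, not a detail left to another document, and it conflicts with the conclusion that the Discussion expects.

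**Conclusion.** The point holds as a conditional one. Sections 2.4 and 2.6 and the Discussion do not fix the same comparator for tiered screening, and no joint analysis of the three strategies is stated. If tiered is judged against routine alone, and routine versus none is above the threshold, tiered can be called cost-effective when no screening has the higher net benefit. If both steps fall below the threshold, the decision is right.

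The size cannot be derived from the protocol. On assumed inputs the gap between the two probabilities runs from large (1.00 against 0.29; 0.82 against 0.26) to small where routine is good value (0.64 against 0.60) or the threshold is high (0.95 against 0.93). It would be too strong to say that the plan will reverse the policy conclusion. It leaves that possibility open on a question listed among the main objectives. The plan should be changed; the sample size is not affected.

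**What to change.** - In section 2.4, replace the sufficiency sentence with a statement that all three strategies will be compared with one another.
- In section 2.6, specify a full incremental analysis: rank the strategies by observed cost, remove dominated and extendedly dominated ones, and report ICERs along the remaining frontier.
- Report tiered versus no screening explicitly, for cost per case detected and for cost per QALY.
- Draw acceptability curves for all three strategies together, each giving the probability of having the highest net benefit, from the same bootstrap or model draws.

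This changes analysis wording only and needs no new data or participants. The one small downside is that the stated probability for tiered screening may look less favourable.

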### Quality control, data management and supervision

2.7

The quality control and supervision of this study involve the following points:

(1) Prior to study initiation, standardized operating procedures (SOPs) are formulated for visual acuity testing, IOP measurement, fundus photography, and ocular optical biometry at community-based physical examination centers. All examiners will undergo standardized training on these protocols and are required to demonstrate competencies through formal assessment before being permitted to participate in the study.(2) The original data of examinations including visual acuity, IOP, and optical biometry will be retained for storage in the disease-specific database of the cohort study office, West China Hospital of Sichuan University. At least two researchers complete the form entry and checking work.(3) Fundus photographs are initially interpreted by experienced physicians holding a rank of attending physician or higher. Then, these assessments are compared with AI-based image analyses. Regarding discrepancy between the human and AI interpretations, the images will be referred to a glaucoma specialist for arbitration, with the expert’s judgment serving as the gold standard.(4) Automated perimetry and RNFL thickness measurements are served as definitive diagnostic tests, with all results being evaluated and confirmed by a glaucoma specialist whose judgment constitutes the gold standard.(5) All screening instruments and follow-up questionnaires would be reviewed by dedicated personnel. If there are incomplete filling out of forms or questionable responses, immediate follow-up contacts will be initiated for verification.(6) A central database is planned to be established and all data can be uploaded to the central database through the researchers in a timely manner, or directly through the inspection equipment via Internet.(7) The study involves a prolonged follow-up period, during which participant attrition is anticipated. The initial sample size calculation has taken an estimated loss-to-follow-up rate (20%) into consideration by expanding sample size. Furthermore, multiple strategies will be employed to enhance participant compliance, including simplifying questionnaire content to reduce response burden, shortening examination duration, and providing subsidies (financial support provided to cover or offset costs associated with the screening process, such as transportation expenses) as necessary. Additionally, active reattempts are made to contact participants lost to follow-up to determine reasons for withdrawal and minimize attrition wherever possible.

### Patient and public involvement no patient or public involvement

2.8

### Statistical analyses

2.9

All statistical analyses will be performed using SPSS V25.0 (IBM, United States) and R software. Continuous variables will be expressed as Mean ± Standard Deviation (SD) or Median with Interquartile Ranges (IQRs), depending on the data distribution, while categorical variables will be presented as frequencies and percentages. Descriptive statistics will be used to summarize the baseline characteristics of each cohort.

Given the cluster randomized design of this study, all between-group comparisons will account for clustering effects. The comparison of the glaucoma detection rate as the primary endpoint will be analyzed using generalized estimating equations (GEE). The GEE model will employ a binomial distribution family and a logit link function, with study group as a fixed effect and community as the clustering variable, adopting an exchangeable working correlation matrix to adjust for within-community correlation. Comparisons of sensitivity and specificity will similarly be conducted using GEE to correct standard errors and confidence intervals (CIs). Cox proportional hazards regression and logistic regression analyses will incorporate cluster as a clustering variable or random intercept to identify risk factors associated with glaucoma incidence. Pearson’s χ^2^ test is utilized only for preliminary comparisons without adjustment for clustering, and final conclusions will be based on results accounting for clustering effects. A two-sided *p* < 0.05 will be considered statistically significant.

For missing data, the pattern, frequency, and possible causes of missingness will first be described. Baseline characteristics of participants with and without complete data will be compared to assess the missing data mechanism (whether missing at random). Primary outcome analyses will be performed using multiply imputed datasets, with complete-case analysis serving as a sensitivity analysis. For participants lost to follow-up after screening, sensitivity analyses using inverse probability weighting will be conducted to evaluate the potential impact of attrition on the estimation of the primary outcomes.

Additionally, the cost-effectiveness analysis will adopt ICER as the economic evaluation measure, with estimated CIs using nonparametric bootstrapping. The sensitivity, specificity, and AUC of physician-based versus AI-assisted image interpretation will be calculated and compared, and differences in AUC will be assessed by the DeLong test or bootstrapping.

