All participants who enter the Tier 3 screening stage will undergo further examinations for definitive diagnosis, including standard automated perimetry for visual field testing, optical coherence tomography (OCT) imaging of retinal nerve fiber layer (RNFL) thickness, and gonioscopy to distinguish open-angle from angle-closure glaucoma. The final diagnosis will be made independently by two glaucoma specialists following a comprehensive review of all clinical data, with reference to internationally accepted diagnostic criteria for glaucoma, namely the presence of characteristic glaucomatous optic neuropathy with corresponding visual field defects, after excluding other ocular or neurological conditions that may cause optic neuropathy. Any diagnostic disagreement between the two specialists will be resolved by a third senior glaucoma expert who will make a final determination. To correct for verification bias, a random sample of 10% of participants who are screen-negative will also be recalled to undergo the same reference standard examination. Sensitivity and specificity of the two screening strategies will be calculated based on all screen-positive participants and the randomly selected screen-negative subset, with appropriate weighting to account for the sampling fraction.

The study is scheduled to begin patient enrollment in October 2025, with follow-up and final data collection expected to be completed in December 2032.

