### Sample size estimation

2.5

The sample size calculation is based on the between-group comparison of glaucoma detection rate, which is the main endpoint of this study. Assuming that the glaucoma detection rate in the routine screening arm would approximate the reported glaucoma prevalence [approximately 3.54% (1, 19)], and that the tiered screening arm, through an optimized screening pathway, would achieve an increased detection rate of 4.54%, corresponding to a difference in detection rate (*Δp*) of 1%. Using this comparison (tiered screening versus routine screening), with a two-sided significance level of α = 0.05 and statistical power of 1 − β = 0.80, the minimum required sample size is calculated to be 6,283 participants per arm. This computation was performed using G*Power (version 3.1.9.7), employing the module for two independent proportions based on Fisher’s exact test.

The sample size is further adjusted for the cluster randomized design by applying a design effect (DEFF). Unlike chronic conditions substantially influenced by behavioral or lifestyle factors, the prevalence of glaucoma is predominantly driven by non-modifiable risk factors such as age and genetic susceptibility. Consequently, between-cluster variation in glaucoma prevalence is expected to be minimal across communities with similar demographic structures. We therefore assumed an intracluster correlation coefficient (ICC) of 0.005 (20) and an average cluster size of 40 participants, which yielded a DEFF of 1.195, approximated as 1.20, resulting in an adjusted requirement of 7,540 participants per arm. In addition, factoring in an anticipated loss-to-follow-up rate of 20%, the final required sample size increases to 9,425 participants per group (totally 28,275 participants in three groups, with *k* = 1).

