### Follow-ups and outcome variables

2.6

Commencing at study initiation, participants will be prospectively followed up annually for a minimum of 6 years. Data will be collected yearly through IOP measurements, fundus photography, and follow-up questionnaires (Table 1). For patients with suspected or confirmed glaucoma, additional data will be collected including ocular optical biometry, RNFL thickness, and automated perimetry. Long-term follow-ups will track annual incidence and blindness rates of glaucoma, and quality of life among glaucoma patients.

**Table 1 tab1:** Follow-up schedule.

Groups		Visit number	0	1	2	3	4	5	6
		Visit time (year)	Baseline	1	2	3	4	5	6
No screening group		Questionnaire	×	×	×	×	×	×	×
Routine screening group		Questionnaire	×	×	×	×	×	×	×
		Intraocular pressure	×			×			×
		Fundus photography	×			×			×
Tiered screening group	High-risk population	Questionnaire	×	×	×	×	×	×	×
		Intraocular pressure	×	×	×	×	×	×	×
		Fundus photography	×	×	×	×	×	×	×
		Glaucoma specialist examination	Performed according to the screening results						
	Non-high-risk population	Questionnaire	×	×	×	×	×	×	×
		Intraocular pressure							
		Fundus photography							

All primary outcome measures will be analyzed on a per-participant (per-person) basis. The main endpoint of this study is glaucoma detection rate of the screening protocol, with sensitivity and specificity of the screening included as additional primary outcome measures. Glaucoma detection rate is defined as the proportion of participants in each arm with a final confirmed diagnosis of glaucoma in at least one eye, as determined by the reference standard examination in the screening arms or by passive case-finding through medical records in the control arm. Sensitivity is defined as the proportion of participants with confirmed glaucoma in at least one eye (as determined by the reference standard comprehensive ophthalmic examination) who are correctly identified by the screening protocol. Specificity is defined as the proportion of participants with no glaucoma in either eye who are correctly classified as negative by the screening protocol.

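### For sensitivity and specificity, the plan's GEE most naturally carries an exchangeable working correlation while the verification weights depend on the test result; an independence working correlation would avoid a possible bias, chiefly in specificity

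*Protocol article*

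**What the plan says.** Section 2.9 (Statistical analyses) sets a binomial, logit-link GEE for the detection rate, clustered by community, and the text then runs on into the accuracy outcomes: "adopting an exchangeable working correlation matrix to adjust for within-community correlation. Comparisons of sensitivity and specificity will similarly be conducted using GEE". The purpose given for the second GEE is to put the standard errors and intervals right. The section names no other working correlation and does not say how sampling weights enter the model.

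Section 2.2 (Study design) defines the verified sample. Everyone who screens positive goes to the reference standard, and "a random sample of 10% of participants who are screen-negative will also be recalled to undergo the same reference standard examination". Both accuracy measures are then computed from these two groups taken together, "with appropriate weighting to account for the sampling fraction".

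Section 2.6 gives these measures high status, "with sensitivity and specificity of the screening included as additional primary outcome measures". The only between-community correlation in the document is the "intracluster correlation coefficient (ICC) of 0.005" in section 2.5, where it is justified by how little glaucoma prevalence should vary between communities.

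**The concern.** In a specificity model the outcome is whether a person without glaucoma screened negative; in a sensitivity model it is whether a person with glaucoma screened positive. Both the chance of being verified and the weight (1 or 10) are therefore functions of the outcome. Weighting repairs outcome-dependent sampling when each weighted residual enters the estimating equation on its own, which is what an independence working correlation does. An exchangeable matrix also scales each community by a factor that falls with the number of people verified there. That number is larger where more people screened positive, so communities with many false positives count for less and specificity is pulled upwards. More communities do not remove the error.

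At stake are the arm-level values of two additional primary outcomes and the coverage of their intervals. If the spread of false positives differs between arms, the comparison of tiered with routine screening is affected as well.

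**Working it through.** **Inputs from the document.** Average cluster size 40; 7,540 analysable participants per arm; prevalence about 3.54%; screen-negatives verified at 10%. The sample-size chain reproduces: 6,283 per arm with continuity correction; design effect 1 + 39 × 0.005 = 1.195, rounded to 1.20; 6,283 × 1.20 = 7,540; 7,540 / 0.8 = 9,425. It is not affected by this point. The document states no figure for the accuracy outcomes.

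**Derived.** Communities per arm: 7,540 / 40 = 188.5 (9,425 / 40 = 235.6 before losses). Non-cases per community: 40 × (1 − 0.0354) = 38.6.

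**Assumed.** True sensitivity, true specificity and the ICC of the test result given disease status are not in the document. Specificity of 90% and 95%, sensitivity of 60% to 80%, and ICC from 0 to 0.05 were tried.

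**Formula.** For one arm, in the form in which weights multiply the residuals, the exchangeable estimate is

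p = Σ c_i Σ w_ij y_ij / Σ c_i Σ w_ij, with c_i = 1 / (1 + (n_i − 1)ρ),

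where n_i is the number of non-cases verified in community i. Independence sets every c_i to 1.

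**Hand example, using expected counts.** Let half the communities have specificity 95% and half 85%. The mean is 90% and the implied ICC is 0.05² / (0.9 × 0.1) = 0.028. Take ρ = 0.42, the working correlation that simulation returns at 90% specificity even when the true ICC is zero, because the outcome-dependent sample distorts it.
- 95% communities: n = 38.6 × 0.05 + 0.1 × 38.6 × 0.95 = 1.93 + 3.67 = 5.60; c = 1 / (1 + 4.60 × 0.42) = 0.341.
- 85% communities: n = 5.79 + 3.28 = 9.07; c = 1 / (1 + 8.07 × 0.42) = 0.228.
- The weighted total is 38.6 in each, so p = (0.341 × 0.95 + 0.228 × 0.85) / (0.341 + 0.228) = 0.910.

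The estimate is 91.0% where the truth is 90%. With no true spread between communities, the same form returns 90.0% despite the inflated ρ: real between-community variation is needed.

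**Simulation of specificity** (beta-binomial communities, 38.6 non-cases each, correlation estimated, 200,000 communities so that sampling error is negligible):

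| True specificity | Independence | Exchangeable, ICC 0.005 | ICC 0.02 | ICC 0.05 |
|---|---|---|---|---|
| 90% | 90.0% | 90.2% | 90.6% | 91.6% |
| 95% | 95.0% | 95.1% | 95.4% | 95.9% |

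At about 236 communities the sampling SD for a true 90% is 0.4, 0.5 and 0.6 points at the three ICCs. The bias is therefore about 0.2 / 0.4 = 0.5, 0.6 / 0.5 = 1.2 and 1.6 / 0.6 = 2.7 SDs. At 188 communities, coverage of the nominal 95% interval for one arm falls to about three-quarters at ICC 0.02 and about one-quarter at 0.05; independence keeps 94% to 95%.

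**Sensitivity.** Few false negatives are verified: 9,425 × 0.0354 × 0.2 × 0.1 = 6.7 per arm at 80% sensitivity, and 9,425 × 0.0354 × 0.4 × 0.1 = 13.3 at 60%. The sampling SD is about 6 to 7 points. In a two-arm fit at ICC 0.05 the estimates move from 80.8% and 70.0% under independence to 80.3% and 69.3%.

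**Between-arm comparison of specificity.**
- Same ICC in both arms, truth 90% v 95% (log odds ratio ln 19 − ln 9 = 0.747): independence v exchangeable gives 0.744 v 0.748, 0.752 v 0.765 and 0.733 v 0.759 at ICC 0.005, 0.02 and 0.05, with SD 0.09 to 0.11. With equal true specificity the log odds ratio stays within 0.003 of zero.
- Different ICCs, both arms truly 90%: at 0.005 v 0.02 the arms come out at about 90.1% and 90.7%. False rejection at nominal 5% is about 9.5%; at 0.02 v 0.05 it is about 20%. Independence stays at about 5%.

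**The case against.** Four objections have force.

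*Exchangeable is not stated for these models.* It is carried over by the word *similarly*. The sentence also gives GEE the role of correcting standard errors and intervals, while section 2.2 has the measures calculated with weights. One could read that as a weighted point estimate plus a cluster-corrected variance, which is close to the remedy below. This stands in part: a reader might infer that the protocol expressly prescribes an exchangeable matrix for the accuracy outcomes, and it does not. But exchangeable GEE is the only structure described, and the sentence follows directly from it.

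*The bias is negligible at the only ICC in the document.* True at 0.005. That value is, however, argued from prevalence. Variation in false-positive results between communities is a different quantity, and the document gives no value for it. The values 0.02 and 0.05 are assumptions.

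*The comparison survives.* A reader might infer that the tiered-versus-routine test is necessarily distorted. The calculations do not support that: with a common ICC the contrast is nearly unchanged and no false difference appears. What remains is the case of unequal ICCs, which is possible because one arm filters by questionnaire and the other does not.

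*The larger figures depend on a weight convention.* If software places the weights inside the variance and the correlation is held at the true ICC, 90% becomes 90.5%, 91.8% and 94.4%. With the correlation estimated, that form gives no valid specificity solution, a failure an analyst would notice. Nor were SPSS or R, the named packages, tested. These figures should not carry the argument.

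**Conclusion.** The point holds in a limited form. Result-dependent weights combined with a non-independence working correlation give a bias in arm-level specificity that does not shrink with trial size: for a true 90%, about 0.2, 0.6 and 1.6 points at ICC 0.005, 0.02 and 0.05. This rests on reading *similarly* as exchangeable, on an assumed ICC for the test result, and on weights multiplying the residuals. The shift in sensitivity is well inside its sampling error. The between-arm comparison is materially biased only if the spread of false positives differs between arms.

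The stronger conclusion, that two primary outcomes are invalid as planned, is not supported: the protocol does not fix the harmful combination in so many words, and at its own ICC the effect is negligible. This is a cheap improvement, not a must-fix.

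**What to change.** Leave the exchangeable GEE for the detection rate. In section 2.9, add one sentence for the accuracy outcomes, for example: sensitivity and specificity will be estimated and compared with inverse-sampling-probability weights (1 for screen-positives, 10 for sampled screen-negatives), an independence working correlation (or the equivalent weighted ratio estimator), and cluster-robust standard errors by community. Carry the same sentence into the statistical analysis plan.

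No data collection or sample size changes. Clustering is still allowed for through the robust variance, as section 2.9 requires of all between-group comparisons. The cost is at most a small loss of efficiency.
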